### Sample size

#### Intervention refinement

The number of qualitative interviews conducted with women who have experienced DVA and professionals will be determined by the point at which thematic saturation is achieved, where further interviews are not expected to add additional information to the themes generated during the concurrent analysis. This is likely to include between 20 and 30 participants.

#### Feasibility trial

The required sample size is based on the precision for estimating the proportion (30%) of eligible participants consenting to participate in the study. If 120 eligible women are screened, then a true recruitment rate of 30% (= 36 recruits) will be estimated as between 21.8 and 38.2%, with 95% probability. This estimate is based on a previous trial that successfully recruited women from one of the collaborating DVA services [27, 52]. Based on previous trials of psychological interventions for women who have experienced DVA [27, 28] up to 33% of the consented and randomized participants are expected to drop out before the start of the mindfulness group/control intervention. Therefore, 54 will be randomized in order to be left with 36 who will be allocated to the intervention or control arm. We will compare the rate of drop out before starting mindfulness/control interventions between the two arms of the trial.

Retention will be optimized using established methods for trials involving women who have experienced DVA, [53–55] further modified through previous research in the UK context [56, 51], which resulted in 70–81% retention rates. The methods include maintaining a safe contact list, reimbursement for travel, childcare and £20 shopping voucher for each treatment session attended.

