#### Feasibility trial

Participants will be recruited through convenience sampling from a pool of service users in collaborating third sector organizations providing health and social care to DVA victims and survivors. The participants will be recruited in cohorts during a 2-month time-frames prior pre-scheduled TI-MBCT group dates:
Near the time of exit from the service, support workers will approach women at individual sessions with study information and invitationsGroup work facilitators will approach women at the end of the group with study information and invitationsAfter women exit the service, support workers will approach them during a 6-month follow-up phone call with study information and invitationsInvitations will be sent to women from the waiting list of the agency services.

All service users undergo risk assessment within the service by their support workers. Support workers will carry out initial screening (Table 2). Those meeting the criteria and willing to be contacted by the study researcher will be referred to the study for final screening (Table 2). Participants will receive the participant information sheet and consent form in advance, and the study researcher will obtain informed written consent.

Randomization will be independent of the study researcher. Once informed consent has been secured and baseline data has been collected, the researcher will telephone a remote randomization service at the Bristol Randomised Trial Collaboration (BRTC) to ascertain the participant allocation: either to the intervention arm (mindfulness) or control arm (IAPT) in a 2:1 ratio, so that each participant has a 2/3rd’s probability of receiving the mindfulness intervention. The participant will be informed which arm she is assigned to by the researcher. Randomization will happen in blocks of 6. For every 18 participants that are randomized, we anticipate that six will drop out before the start of the intervention, four will continue in the study as controls and eight will continue in the study in the intervention arm—this will be sufficient to run a mindfulness group.

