#### Feasibility outcomes

Table 4 summarizes feasibility outcomes that will be used in the *feasibility trial* to evaluate the feasibility of a future full-size trial.

**Table 4 Tab4:** Feasibility outcomes

Outcome	Description; measure
Recruitment/randomization rate	Proportion of participants randomized into two arms; the denominator will be the number of participants eligible for recruitment/randomization
Intervention uptake	Proportion of participants who took up the TI-MBCT or self-referred to the IAPT service; the denominator will be the number of participants randomized in the arm, respectively.
Intervention retention	Proportion of participants in the intervention arm who received the “minimum dose” of the intervention, four sessions of mindfulness intervention [29].
Follow-up rate	Proportion of participants followed up and providing outcome data at six months post-randomization out of those enrolled in the trial. The proportion who have been lost to follow-up will also be calculated by the trial arms.
Participant experience	Participant views on the acceptability of the intervention and trial design.

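### The sample-size paragraph uses 36 both before and after drop-out, so 54 randomised cannot come from 120 eligible women at 30% consent

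*Protocol article*

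**What the plan says.** Under Sample size, Feasibility trial, the protocol article bases the required number on the "precision for estimating the proportion (30%) of eligible participants consenting to participate in the study". The calculation reads: "If 120 eligible women are screened, then a true recruitment rate of 30% (= 36 recruits"), and this rate "will be estimated as between 21.8 and 38.2%, with 95% probability".

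The paragraph then brings in early loss: "up to 33% of the consented and randomized participants are expected to drop out before the start of the mindfulness group/control intervention". From that it concludes: "Therefore, 54 will be randomized in order to be left with 36 who will be allocated to the intervention or control arm".

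Three other places bear on how these steps connect:

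- Recruitment and consent, Feasibility trial, fixes the order of events: "Once informed consent has been secured and baseline data has been collected, the researcher will telephone a remote randomization service". The same section gives the expected loss per cohort: "For every 18 participants that are randomized, we anticipate that six will drop out before the start of the intervention", with eight women continuing in the intervention arm and four as controls.
- Table 4 defines the recruitment/randomisation rate: "Proportion of participants randomized into two arms; the denominator will be the number of participants eligible for recruitment/randomization".
- Study design, Feasibility trial, plans two mindfulness groups, one after the other. Table 3 caps a group at nine women.

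**The concern.** The number 36 appears at two stages that are separated by a one-third loss. In the precision step it is the number who consent. In the drop-out step it is the number left after women who have already consented and been randomised fall away. The two could coincide only if nobody dropped out, and the paragraph assumes up to 33% will.

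Recruitment is one of the main questions of this study, so its planning figures need to be usable. As written, a team that approaches 120 eligible women and achieves exactly the assumed 30% has 36 randomised: on plan for the rate, yet 18 women (one third) short of the stated 54. A team that continues until 54 are randomised needs a screening pool that the protocol does not mention, and the stated interval no longer describes its estimate.

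The last clause of the 54/36 sentence adds a smaller problem. It describes the women remaining after drop-out as those still to be allocated, whereas the recruitment section makes allocation the act of randomisation, before the drop-out occurs.

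**Working it through.** **Inputs.** Eligible women 120, consent rate 0.30, 95% confidence, drop-out 0.33, 54 randomised and 36 left (all from Sample size, Feasibility trial). Allocation 2:1, and 18 randomised giving 8 intervention and 4 control women continuing (Recruitment and consent). Two groups (Study design). At most nine women per group (Table 3).

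**Step 1: each stated figure reproduces on its own.**

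- Consenters: 120 × 0.30 = 36.
- Wald interval: 0.30 ± 1.96 × √(0.30 × 0.70 / 120) = 0.30 ± 0.082, or 21.8 to 38.2%. This matches. Wilson (22.5 to 38.7%) and Clopper-Pearson (22.0 to 39.0%) do not, so the authors used Wald.
- Drop-out inflation: 36 / (1 − 0.33) = 53.7, rounded up to 54. This matches.

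**Step 2: join the two steps.** The protocol's order is eligible → consented → randomised → started. So randomised = eligible × consent rate, and started = randomised × (1 − drop-out).

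- *Forward from 120:* 120 × 0.30 = 36 randomised; 36 × 0.67 = 24.1, about 24 starting. The paragraph says 36 are left.
- *Backward from 36 left:* 54 randomised; 54 / 0.30 = 180 eligible. The paragraph says 120. The gap is 60 women, 50% more screening.
- *Holding 120 and 54 fixed:* 54 / 120 = 45% consent. The paragraph says 30%, with an upper limit of 38.2%. Under the Table 4 definition, 45% is the rate the trial would report. At a true rate of 30%, the exact binomial probability of 54 or more consenters among 120 is about 0.0004.

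**Step 3: precision if 54 is kept.** 0.30 ± 1.96 × √(0.21 / 180) = 0.30 ± 0.067, or 23.3 to 36.7%.

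**Step 4: compare both chains with the delivery plan.**

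| | 36 randomised | 54 randomised |
|---|---|---|
| Eligible at 30% | 120 | 180 |
| 95% interval for 30% | 21.8–38.2% | 23.3–36.7% |
| Allocated 2:1 | 24 and 12 | 36 and 18 |
| Starting after one-third loss | 16 and 8 | 24 and 12 |
| Cohorts of 18 | 2 | 3 |
| Places in two groups of nine | 18, enough for 16 | 18, too few for 24 |

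The two planned groups, at 18 randomised per group, give 2 × 18 = 36. The delivery plan therefore fits 36 randomised and does not fit 54. The green recruitment threshold in Table 1, 24 recruited over 6 months, matches neither figure.

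**The case against.** The best defence is that the 120 is conditional: it illustrates how precisely a 30% rate would be estimated and does not cap screening. Nothing in the protocol says recruitment stops at 120, and the one operational statement is that 54 will be randomised. On that reading the trial simply screens more women. The precision then improves (half-width 6.7 points instead of 8.2), so the stated interval errs on the cautious side. No power claim or hypothesis test depends on it, and the numerical recruitment criterion in Table 1 is a count that uses none of 120, 30%, 36 or 54. The per-cohort figures are also sound in themselves: 18 randomised with 12 continuing, multiplied by three, is 54 and 36.

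Part of this stands. It is not certain that a team would stop at 36, and the error has not been shown to alter a progression decision. The per-cohort sentence is not itself wrong. Table 4 already counts intervention uptake over all women randomised to the arm, so the loose wording about allocation does not spread to that denominator.

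The core survives. The paragraph says the required sample size rests on the 120-woman calculation, and no other screening number or consent rate appears anywhere. Taking recruits to mean women who start treatment does not help either, because the 30% is defined as the proportion consenting and the loss is placed after consent and randomisation. Even if 120 is only an illustration, the screening workload for 54 is left unstated and 54 still exceeds the two-group plan.

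**Conclusion.** The paragraph is wrong as written. Its two calculations are each correct, but they use one number for two different stages. With 30% consent and 33% loss before treatment starts, 120 eligible women yield 36 randomised and about 24 starting. To have 36 starting, 54 must be randomised from 180 eligible women. The discrepancy is 18 randomised women or 60 screened women, depending on which end is held fixed.

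This rests on the protocol's own 30% and 33% and on its stated order of consent before randomisation. The 33% is given as an upper figure; a lower loss would narrow the gap, but only zero loss would close it. The consequence is an ambiguous target and an understated screening effort in a study meant to measure recruitment. No inferential error follows, since the analysis is descriptive.

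**What to change.** State one chain from eligible women to women starting, with drop-out applied after randomisation. Either version is consistent:

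1. **Keep 120 eligible.** 30% consent (95% interval 21.8 to 38.2%), 36 randomised 2:1 (24 TI-MBCT, 12 IAPT), about 24 starting (16 and 8). This fits the two groups in Study design combined with the cohort of 18 in Recruitment and consent. The cost is a smaller sample, so the outcome standard deviations wanted for the definitive trial would be estimated less precisely.
2. **Keep 54 randomised.** 180 eligible women, 95% interval 23.3 to 36.7%, allocated 36 and 18, about 36 starting (24 and 12). The cost is 60 more eligible women to screen. The number and size of mindfulness groups must then be reconciled with 24 intervention starters.

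The choice is the sponsor's. In either case, reword the end of the 54/36 sentence so that it refers to women starting their allocated intervention, because allocation has already happened at randomisation. It would also help to say how the Table 1 recruitment threshold of 24 relates to the chosen target. The edit itself is a few restated figures.

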### Recruitment and consent

#### Intervention refinement

Women who have experienced DVA and professional stakeholders will be recruited through existing professional networks, previous study databases, and snowballing techniques. Participants will be sent the participant information sheet and consent form in advance, and written, or verbal, informed consent will be recorded.

#### Feasibility trial

Participants will be recruited through convenience sampling from a pool of service users in collaborating third sector organizations providing health and social care to DVA victims and survivors. The participants will be recruited in cohorts during a 2-month time-frames prior pre-scheduled TI-MBCT group dates:
Near the time of exit from the service, support workers will approach women at individual sessions with study information and invitationsGroup work facilitators will approach women at the end of the group with study information and invitationsAfter women exit the service, support workers will approach them during a 6-month follow-up phone call with study information and invitationsInvitations will be sent to women from the waiting list of the agency services.

All service users undergo risk assessment within the service by their support workers. Support workers will carry out initial screening (Table 2). Those meeting the criteria and willing to be contacted by the study researcher will be referred to the study for final screening (Table 2). Participants will receive the participant information sheet and consent form in advance, and the study researcher will obtain informed written consent.

Randomization will be independent of the study researcher. Once informed consent has been secured and baseline data has been collected, the researcher will telephone a remote randomization service at the Bristol Randomised Trial Collaboration (BRTC) to ascertain the participant allocation: either to the intervention arm (mindfulness) or control arm (IAPT) in a 2:1 ratio, so that each participant has a 2/3rd’s probability of receiving the mindfulness intervention. The participant will be informed which arm she is assigned to by the researcher. Randomization will happen in blocks of 6. For every 18 participants that are randomized, we anticipate that six will drop out before the start of the intervention, four will continue in the study as controls and eight will continue in the study in the intervention arm—this will be sufficient to run a mindfulness group.

Allocation concealment will be achieved using the remote randomization service acting as a “third party” to assign the participant to either intervention or control arms. This ensures that the study researcher, enrolling and consenting participants, cannot be influenced by knowledge of their expected allocation at this stage. Once the participant has been allocated to either the intervention or the control arm, this assignment will be made available to the researcher. This is to enable the participant’s details to be passed onto the mindfulness teacher if they are in the intervention arm. The mindfulness teacher will invite the prospective intervention participants to an orientation meeting followed by an individual telephone assessment. Those participants randomized to the control arm will be advised by the study investigator how to self-refer to the IAPT service and helped with the self-referral if needed and wanted.

Due to the psychological nature of the intervention in both trial arms, it will not be possible to blind participants to details of which arm they have been allocated. Due to funding limitations, the same study researcher will carry out recruitment, baseline, and follow-up assessments, and monthly check-up calls; therefore, it will not be possible to blind the study investigator to the treatment groups. All process evaluation and analysis will be conducted by a different researcher blind to the participation group.

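### With fixed blocks of 6 at 2:1 and one researcher who receives every allocation, about 29% of allocations can be deduced in advance, so the protocol's assurance of concealment does not hold as worded

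*Protocol article*

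**What the plan says.** All of this stands in the protocol article under Recruitment and consent, Feasibility trial.

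- Block size: "Randomization will happen in blocks of 6". No other size is given, and nothing says that the size varies or is withheld.
- Ratio: allocation is "in a 2:1 ratio, so that each participant has a 2/3rd’s probability of receiving the mindfulness intervention". A block of 6 therefore holds four TI-MBCT and two IAPT places.
- Who learns the result: after consent and baseline data, "the researcher will telephone a remote randomization service". Then, "The participant will be informed which arm she is assigned to by the researcher".
- Who does the work: "the same study researcher will carry out recruitment, baseline, and follow-up assessments, and monthly check-up calls", and as a result "it will not be possible to blind the study investigator to the treatment groups".
- The claim about the remote service: "This ensures that the study researcher, enrolling and consenting participants, cannot be influenced by knowledge of their expected allocation at this stage".

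Support workers carry out the initial screening and refer women on. The study researcher enters at final screening.

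**The concern.** A remote service protects the list. It cannot protect a sequence whose block size is fixed and printed when the person enrolling hears every result. Once two IAPT or four TI-MBCT places have appeared in a block, the rest of that block is settled, and the sixth place is settled in every block.

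Two common sources of dilution are absent. There is one recruiter, who sees the whole sequence, not several who each see a part. That recruiter also cannot be kept unaware of results.

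At stake is whether the two arms stay comparable. Between referral and the telephone call the researcher conducts final screening, consent and the baseline meeting. Someone who knows or strongly suspects the next arm could, without any intent, present the study differently or book a meeting sooner or later. The results exposed are the between-arm differences in means with 95% confidence intervals (Quantitative analysis) and the comparison of drop-out before the start of treatment between arms (Sample size, Feasibility trial).

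**Working it through.** **The plan's own figures.** The article gives no figure for predictability. Its numbers for randomization do reproduce: 36 / (1 − 1/3) = 54 women, which is 54 / 6 = 9 complete blocks. Per 18 randomized, 18 × 1/3 = 6 drop out, and the remaining 12 split 2:1 into 8 and 4, as stated.

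**Inputs.** Block of 6 with 4 TI-MBCT and 2 IAPT, 54 randomized, and every allocation revealed to the researcher in turn. The researcher is assumed to know the block size and to keep a tally.

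**Certain allocations.** There are C(6,2) = 15 equally likely orders. A place is certain when one arm is already used up.

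| Place in block | Orders in which it is already certain | Probability |
|---|---|---|
| 1 | 0 of 15 | 0 |
| 2 | 0 of 15 | 0 |
| 3 | 1 of 15 | 6.7% |
| 4 | 3 of 15 | 20.0% |
| 5 | 7 of 15 | 46.7% |
| 6 | 15 of 15 | 100% |

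Sum: (1 + 3 + 7 + 15) / 15 = 26/15 = 1.733 places per block, and 1.733 / 6 = 28.9%.

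Closed form, by arm, with a = 4 and b = 2:

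- certain TI-MBCT places = a/(b + 1) = 4/3
- certain IAPT places = b/(a + 1) = 2/5
- total = 4/3 + 2/5 = 26/15, which agrees.

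Over 9 blocks: 9 × 26/15 = 15.6 of 54, made up of 9 × 4/3 = 12.0 TI-MBCT and 9 × 2/5 = 3.6 IAPT.

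**Best guess.** Guess whichever arm has more places left, counting ties as half. Over the 15 × 6 = 90 places this is right in 67, or 74.4%. Always guessing TI-MBCT is right in 60 of 90, or 66.7%. The gain is 7/90 = 7.8 percentage points, or 54 × 7/90 = 4.2 women.

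**Alternatives.** For varying sizes, trials of 54 were simulated with a researcher who knows the possible sizes but not their order. The fixed sizes are exact.

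| Scheme at 2:1 | Certain | Best guess right |
|---|---|---|
| Fixed 6 (stated) | 28.9% | 74.4% |
| Fixed 9 | 21.4% | 72.8% |
| Fixed 12 | 17.0% | 71.7% |
| Varying 3, 6 | 9.9% | 75.5% |
| Varying 6, 9 | 5.3% | 72.9% |
| Varying 3, 6, 9 | 3.7% | 73.6% |

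Varying sizes remove most of the certainty. They lower best-guess accuracy only slightly, and that figure assumes a recruiter who updates odds optimally from known sizes.

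**Effect on group filling.** With sizes 3, 6 and 9, block boundaries fall on multiples of 3. Only an unfinished block can move the first 18 away from 12:6, and by at most two. A check with 300,000 simulated sequences put the first 18 within one of 12:6 in 99.6%. A later run of 18 can be cut by an unfinished block at both ends. It stayed within one in about 97%, was off by two in about 3%, and was off by three in about 0.1%.

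**The case against.** The strongest reply is that the practical gain to a recruiter is small. Under 2:1 anyone can guess TI-MBCT and be right two times in three, and about 12 of the 15.6 certain places belong to that likelier arm. Only about 3.6 women in 54 would be foreseeable controls. This stands, and it limits the size of the problem.

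Several stronger readings are tempting, and the article does not support them.

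- *Concealment is defeated outright.* About 71% of allocations remain uncertain, the list stays with the service, and the call comes after consent and baseline. The article does not say that the researcher tallies allocations. The places are knowable, which is not the same as known.
- *One person controls who enters.* Support workers and group facilitators approach women, and support workers do the initial screening. They are not described as receiving allocations. The researcher's influence begins after referral, inside 2-month recruitment windows.
- *The recruitment result is biased.* Table 1 judges recruitment on a total count over 6 months, not by arm. Changing the order of entry does not clearly alter that count.
- *Acceptability of randomization is biased.* It is judged from the process evaluation, which is assigned to a different researcher who is blind to group.
- *The flaw will pass to the definitive trial.* No block size is fixed for that trial, and this stage exists to revise procedures.

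The analysis is also mainly descriptive, with no p values. That lowers the consequence, but it does not protect a difference in means from selective entry.

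A last objection is that blocks of 6 deliver exactly 12:6 in every 18, which the plan uses to fill groups of up to nine. With one-third drop-out, 14 allocated would leave 9.3 and 10 would leave 6.7. Departures of that size are rare under the scheme checked here. A departure of one leaves 13 × 2/3 = 8.7 or 11 × 2/3 = 7.3. The objection is a reason to tell the group organizers, and it does not defeat the change.

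**Conclusion.** The point holds in a limited form. Under the scheme as stated, 28.9% of allocations (15.6 of 54) can be deduced beforehand, and the last place in each block always can. The statement that remote randomization ensures the researcher cannot be influenced by expected allocation is therefore wrong as worded.

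The threat is to comparability of the arms through selection or timing of entry after referral, and so to the between-arm mean differences and drop-out by arm. It is a risk and not a demonstrated bias. It rests on the researcher knowing the printed block size and keeping count, and on the block size not varying. Drop-out before the start of treatment does not reduce it, because the arm is revealed at randomization.

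The change is worth making because it is cheap and the article asserts a protection that the design does not give. In a descriptive feasibility trial it is not a fatal flaw.

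**What to change.** Have the randomization service use randomly varying permuted blocks at 2:1, for example sizes 3, 6 and 9, with sizes and order held by the service and withheld from the researcher. The protocol should say only that block sizes vary. Certain allocations then fall to about 4% even if the possible sizes become known. A larger fixed block is a weaker remedy, since 17% to 21% would remain certain at sizes 12 and 9.

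Reword the concealment sentence to claim what is delivered, along these lines: *the allocation list is held by a remote service and released only after consent and baseline; block sizes vary and are not disclosed to the researcher, which limits the scope for predicting the next allocation.*

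The cost is a changed setting at the service and a protocol amendment, which the article says goes to the Research Ethics Committee. If recruitment has begun, the service should make the switch at the end of a block. The downside is that a cohort of 18 may depart from 12:6, usually by no more than one and rarely by two or more. Best-guess accuracy stays near 74% for an optimal guesser, so the change removes most of the certainty but not all predictability.
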